### Sample size and power

We will randomize n=32 participants to each treatment group and assume 6% of participants will drop out by the end of the study so that there will be n=30 participants in each group at the final endpoint. The power calculations below are based on the second Helmert contrast: TECH vs. STND because this contrast contains the fewest number of subjects (30 in each group) and we expect this contrast to have the smallest effect sizes. The first Helmert contrast: STND and TECH vs. SELF has a larger sample size (60 vs. 30) and we anticipate larger effects sizes in this contrast due to the limited intensity of the SELF intervention. Therefore, by powering the study based on the second contrast, we will have more than adequate power for the first contrast.

#### Weight loss

We measure weight loss at 3, 6, and 12 months. Using data from a previous weight loss trial
[16], we saw standard deviations of 8.4 and 10.7 pounds at months 3 and 6, respectively, with a correlation of 0.86 between the two time points. With 80% power and an n=30 in both groups, we will be able to detect a difference of 6.6 pounds between the two groups.

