### Study aims

Guided by CST and social networks research, the ENGAGED study will evaluate the feasibility and efficacy of a technology-supported weight loss program for obese adults. Specifically, the primary aim of the ENGAGED study is to conduct a three-group randomized controlled trial testing the efficacy of the ENGAGED technology-supported behavioral weight loss program, as compared to the same program delivered using standard paper and pencil self-monitoring, and self-guided behavioral weight loss supported by participants receiving DVD’s depicting DPP treatment. Primary outcomes include: (1) weight loss and (2) behavioral adherence, which is operationalized by (a) self-monitoring of diet and activity and (b) attainment of diet and activity goals. As a secondary outcome, the time spent administering the intervention by lifestyle coaches will also be examined to assess intervention costs. The second aim of the ENGAGED study is to test whether the weight loss in the technology-supported condition is mediated by behavioral adherence to self-monitoring and achievement of diet and activity goals.

We hypothesize that using a theory-guided, technology-supported weight loss treatment will result in clinically significant weight loss with fewer in-person sessions by preserving regular social support, accountability, and feedback via mobile technology. Further, we hypothesize that technology-supported weight loss treatment will result in greater weight loss compared to the traditional paper self-monitoring approach.

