### Data analytic plan

#### Linear mixed modeling

Data will be analyzed on an intent-to-treat basis. The basic modeling approach will entail linear mixed models for longitudinal data. The primary aim is to test for treatment group differences on weight loss at 3-, 6-, and 12-months as well as differences in behavioral adherence and goal attainment at 3- and 6-months. Linear mixed models do not require that participants are measured at all time points, and therefore can include participants with missing data across time. In these analyses, we will examine changes across time by treating time as a nominal variable in the analysis to allow for non-linear trends. In addition to the effect of time, the main independent variable is treatment groups, a between-subjects factor with 3 levels: STND, TECH and SELF. A priori Helmert contrasts
[38] will be used to test the following comparisons at 3- and 6-months: 1) STND and TECH vs. SELF and 2) TECH vs. STND. We will also examine group by time interactions to test whether change in outcome across time differs by group.

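### The 6.6 lb detectable difference matches an average over months 3 and 6, but the plan describes contrasts at each visit; month 6 alone needs 7.7–7.9 lb, and month 12 has no contrast or power figure

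*Protocol article*

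**What the plan says.** Under Sample size and power, the protocol article bases its calculations on the second Helmert contrast, TECH v STND. It randomizes 32 per arm and assumes 6% dropout, so that "there will be n=30 participants in each group at the final endpoint". The Weight loss subsection notes that weight loss is measured at 3, 6 and 12 months. It then gives its inputs from a previous trial: "we saw standard deviations of 8.4 and 10.7 pounds at months 3 and 6, respectively", "with a correlation of 0.86 between the two time points". From these it draws one figure: "With 80% power and an n=30 in both groups", "we will be able to detect a difference of 6.6 pounds between the two groups". No visit is attached to it, and it is not called an average.

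The Linear mixed modeling section says: "The primary aim is to test for treatment group differences on weight loss at 3-, 6-, and 12-months". Time enters as a nominal factor. The a priori Helmert contrasts "will be used to test the following comparisons at 3- and 6-months", and group by time interactions will also be examined. No contrast averaged over visits is described.

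Study aims adds: "Primary outcomes include: (1) weight loss and (2) behavioral adherence". The subsections on diet and physical activity self-monitoring also quote two SDs and a between-visit correlation, followed by one detectable difference each (0.23 and 22%).

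**The concern.** A comparison at one visit does not need the correlation between visits, whereas an average over visits does. Quoting the correlation and then giving one figure with no visit suggests that the power statement describes a pooled comparison, while the analysis section reads as visit-by-visit comparisons. The more variable visit, month 6, would then have less power than the document implies. Month 6 is also the end of the coaching and app period, so a null result there would be read against an 80% assurance that the stated inputs do not give.

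Month 12 is a separate gap. It is in the primary aim, and the 30 per arm is tied to the final endpoint, yet the contrasts and the variance inputs stop at month 6.

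**Working it through.** **Inputs.** From Sample size and power and its subsections: 30 per arm, 80% power, and the SDs and correlations shown below. Assumed: two-sided 5%, since no significance level is stated.

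**Formulas.**
- SD of the two-visit average = √[(s₃² + s₆² + 2·r·s₃·s₆)/4].
- Detectable difference (normal) = (1.960 + 0.842) × SD × √(2/30) = 0.7234 × SD.
- Power for difference d (normal) = Φ(d / [SD·√(2/30)] − 1.960).
- The t results use the noncentral t distribution with 58 degrees of freedom.

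**Step 1: reproduce 6.6 lb.** SD of the average = √[(70.56 + 114.49 + 154.59)/4] = √84.91 = 9.21 lb. Detectable difference = 0.7234 × 9.21 = 6.67 lb (t: 6.78). Power for 6.6 lb = 79.2% (t: 77.9%). This matches the stated figure closely.

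**Step 2: try other routes to 6.6 lb for weight.**
- Root-mean-square of the two SDs: 6.96 lb.
- Simple mean of the two SDs: 6.91 lb.
- Month 6 at one-sided 5%: 6.87 lb.
- Month 3 at two-sided 2.5%: 6.69 lb. This comes close, but the same route gives 0.247 for diet self-monitoring against 0.23 stated.

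**Step 3: apply the averaging formula to the other outcomes.**

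| Outcome | SDs; correlation | Average (normal) | Stated |
|---|---|---|---|
| Diet self-monitoring | 0.31, 0.34; 0.93 | 0.231 | 0.23 |
| Activity self-monitoring | 0.30, 0.33; 0.91 | 0.223 | 22% |
| Activity, min/week | 142, 142; 0.9 | 100.1 | 100 |
| Calories | 498, 431; 0.9 | 328 | 375 |

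Three of the four agree. For activity minutes a single visit would give 102.7. The calorie figure does not agree.

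**Step 4: weight loss by visit.**

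| Visit | SD (lb) | Detectable difference, normal / t (lb) | Power for 6.6 lb, normal / t |
|---|---|---|---|
| Month 3 | 8.4 | 6.08 / 6.18 | 86.1% / 84.9% |
| Month 6 | 10.7 | 7.74 / 7.87 | 66.6% / 65.1% |

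For month 6: 6.6 / (10.7 × 0.2582) = 2.389, and Φ(2.389 − 1.960) = 0.666. At one-sided 5%, power at month 6 would be Φ(2.389 − 1.645), about 77%, still below 80%. Reaching 80% for 6.6 lb at month 6 would take 42 per arm (normal), or 42/0.94, about 45, before dropout.

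**Step 5: self-monitoring at month 6.** Diet: 0.7234 × 0.34 = 0.246 (t: 0.250), against 0.23. Activity: 0.7234 × 0.33 = 0.239 (t: 0.243), against 22%.

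**Step 6: month 12.** No SD is given, so no power can be computed. Purely as illustration, an assumed SD of 10.7 to 13 lb gives power for 6.6 lb from 67% down to 50% (normal).

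**The case against.** The strongest defence is that the contrasts may be meant as a group effect pooled over months 3 and 6, with visit-specific differences left to the group by time interaction that is mentioned next. The correlations quoted in the power section fit that intention. On this reading the calculation and the test agree, and only the wording is unclear. The text does not exclude it, and the averaging is itself inferred from the arithmetic. But no pooled contrast is described, and contrasts placed at 3 and 6 months with nominal time are most naturally read as one per visit. The ambiguity needs settling either way.

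Second, 6.6 lb is what a fixed sample size can detect; it is not an assumed effect or a clinical threshold. That stands. A reader might infer that the trial is too small and must grow, but the document sets no target difference against which that could be judged.

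Third, month 12 is in the mixed model and in the group by time interaction, and some detail may sit in a full protocol or analysis plan that is not shown. That also stands in part: month 12 is not left unanalysed. But the interaction does not supply the named TECH v STND comparison at month 12, and the article itself puts that visit in the primary aim while ending its contrasts at month 6.

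**Conclusion.** The point holds as a mismatch between the power statement and the described tests. The 6.6 lb figure fits the month 3/6 average (6.7–6.8 lb). By visit it is conservative at month 3 (6.1–6.2 lb detectable, about 85% power) and optimistic at month 6 (7.7–7.9 lb detectable, 65–67% power). The self-monitoring figures shift in the same way but only slightly: to 0.25 for diet and 24% for activity at month 6. Month 12 lacks a planned contrast and any power basis despite its place in the primary aim.

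This rests on two-sided 5%, on 30 per arm, and on reading the contrasts as visit-specific.

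Two stronger readings are not supported. One is that 80% power fails at every visit, which month 3 contradicts. The other is that month-12 power is known to be low, which would rest on an SD the document does not give. A reader might also infer a specific inflated false-positive rate from the several primary outcomes and visits. With no stated significance level, and with adherence expected to drive weight loss so that the outcomes are not independent, the document does not support a number.

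**What to change.** Choose one of two routes and say so in both the Linear mixed modeling and Weight loss sections.

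- Define the powered TECH v STND weight contrast as the average over months 3 and 6, and state its detectable difference as 6.7–6.8 lb.
- Or keep the visit-specific contrasts and state 7.7–7.9 lb at month 6 (6.1–6.2 lb at month 3).

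State the significance level used. Label the self-monitoring figures to match: as averages (0.23 and 22%), or as 0.25 and 24% at month 6. On either route, add month 12 to the planned weight contrasts and make no 80% power claim for it.

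The cost is wording and a less favourable stated figure. The sample size, visits and data collection do not change.

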#### Diet self-monitoring adherence

We measure dietary self-monitoring adherence at 3 and 6 months as the ratio of actual days of diet self-monitoring relative to the possible number of days. Using data from a previous trial
[16], we observed a standard deviation of 0.31 and 0.34 at 3 and 6 months, respectively, as well as a correlation of 0.93 between the two time points. Thus, with 80% power and an n=30 in both groups, we will be able to detect a difference in adherence ratios of 0.23 between the two groups.

#### Physical activity self-monitoring adherence

Physical activity self-monitoring will be assessed as the number of days reporting physical activity on paper diaries (STND and SELF) or wearing the accelerometer (TECH), divided by the number of possible days. Data from a previous trial
[16] shows a standard deviation of 0.30 at 3 months and 0.33 at 6 months and a correlation of 0.91 between the two time points. With 80% power and an n=30 in both groups, we will be able to detect a difference in percent adherence of 22% between the two groups.

#### Dietary intake adherence

We measure adherence to calorie goals at 3 and 6 months using 3 day 24 hour recalls. Using pilot data from a previous trial, we observed a standard deviation of change in calories of 498 at month 3 and 431 at month 6, with a correlation of 0.9 between the two time points. With 80% power and an n=30 in both groups, we will be able to detect a calorie reduction difference of 375 calories.

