#### Physical activity adherence

Physical activity adherence is measured by accelerometer at months 3 and 6 as the number of minutes of moderate to vigorous intensity physical activity per week. Using data from a previous trial
[39], we assume a standard deviation of 142 minutes/week at months 3 and 6, with a correlation of 0.9 between the two time points. With 80% power and an n=30 in both groups, we will be able to detect a 100 minute/week difference between the two groups.

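### The detectable calorie difference of 375 does not follow from its own stated inputs, which give about 328; the error is conservative and leaves the sample size unchanged

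*Protocol article*

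**What the plan says.** The Sample size and power section of the protocol article bases all its calculations on one contrast, "TECH vs. STND because this contrast contains the fewest number of subjects (30 in each group"). Dropout is already allowed for in that number: the authors "assume 6% of participants will drop out by the end of the study so that there will be n=30 participants in each group".

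Five subsections then follow one layout: a standard deviation for month 3 and month 6 (or one common to both), a correlation between the visits, 80% power, 30 per group, and a detectable difference. For Dietary intake adherence the inputs are "we observed a standard deviation of change in calories of 498 at month 3 and 431 at month 6" and a correlation of 0.9, and the result is "With 80% power and an n=30 in both groups, we will be able to detect a calorie reduction difference of 375 calories".

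The companion results include "we will be able to detect a difference of 6.6 pounds between the two groups" (Weight loss), "we will be able to detect a difference in adherence ratios of 0.23 between the two groups" (Diet self-monitoring adherence) and "we will be able to detect a 100 minute/week difference between the two groups" (Physical activity adherence). Physical activity self-monitoring adherence has a stated detectable difference of 22%. The section gives no alpha, sidedness or formula.

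**The concern.** Five results in one format should come from one method. Four do, to within rounding or close to it. The calorie result is too large for any reading of its own inputs at the same settings.

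The Study aims section makes attainment of diet goals part of behavioral adherence, which is one of the two primary outcomes. This sentence is the power statement for that component. As printed, a reader cannot tell whether the result is a slip or whether a standard deviation was copied wrongly. In the second case the printed values would understate the variability of calorie change.

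**Working it through.** **Inputs.** Standard deviations 498 and 431, correlation 0.9, 80% power and 30 per group, all from Dietary intake adherence. Two-sided alpha 0.05 is an assumption, tested in step 1.

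**Formula.** Standard deviation of the mean of two visits: SD_avg = √[(s₃² + s₆² + 2·r·s₃·s₆)/4]. Detectable difference: (1.960 + 0.842) × SD_avg × √(2/30).

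**Step 1: the other four figures.**

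| Outcome | s₃, s₆, r | SD_avg | Derived | Stated |
|---|---|---|---|---|
| Weight (lb) | 8.4, 10.7, 0.86 | 9.21 | 6.67 | 6.6 |
| Diet self-monitoring | 0.31, 0.34, 0.93 | 0.319 | 0.231 | 0.23 |
| Activity self-monitoring | 0.30, 0.33, 0.91 | 0.308 | 0.223 | 0.22 |
| Activity (min/week) | 142, 142, 0.9 | 138.4 | 100.1 | 100 |

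All agree within about 1.2%, and power at the stated differences is 79.0% to 79.9%. This supports both the formula and the assumed alpha.

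**Step 2: calories by the same method.** SD_avg = √[(248,004 + 185,761 + 386,348.4)/4] = √205,028 = 452.8. Detectable difference = 2.802 × 452.8 × 0.2582 = 327.5 kcal. The noncentral t distribution with 58 degrees of freedom gives 333.1. The ratio of stated to derived is 375/327.5 = 1.145 (normal) or 375/333.1 = 1.126 (t).

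**Step 3: other readings at the same alpha, power and n.**

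| Standard deviation used | Normal | t |
|---|---|---|
| Month 3 alone (498) | 360.2 | 366.3 |
| Month 6 alone (431) | 311.8 | 317.1 |
| Mean of visits with r = 1.0 (464.5) | 336.0 | 341.7 |

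A weighted average of the two visits, with non-negative weights, cannot have a standard deviation above 498, so no such weighting reaches 375. Solving backwards, 375 needs 375/(2.802 × 0.2582) ≈ 518 (normal) or about 510 (t).

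**Step 4: other settings.** With SD_avg = 452.8:
- 90% power gives 379 kcal, but the other four figures would then be 7.7 lb, 0.267, 0.258 and 116 min/week.
- Alpha 0.0167 gives 378 kcal and moves the other four in almost the same way.
- 23 per group gives 374 kcal, against the stated 30.
- 28 per group with the month 3 standard deviation alone gives 373 (normal) to 380 (t), again against the stated 30.

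**Step 5: power for 375 kcal.** The standardized difference is 375/(452.8 × 0.2582) = 3.21. Power is 88.4% by t (89.4% by the normal approximation). It is 82% with the month 3 standard deviation alone and 91% with month 6 alone, both by t.

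**The case against.** The strongest reply is that the sentence, taken literally, is safe. Under every reading of the printed inputs in step 3, the trial has more than 80% power for 375 kcal. The sample size was fixed at 32 randomized and 30 retained per group before any detectable difference was quoted, so none was derived from 375. Nothing in the Data analytic plan uses the figure. All of this stands, and it limits the consequence. It does not make 375 the difference detectable at 80% power, which is how the section presents it.

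A second reply is that the method is reconstructed. Alpha, sidedness and formula are not printed, weight computes to 6.67 and would round to 6.7, and the close match belongs to the normal approximation. By t the four figures would be 6.78, 0.235, 0.226 and 101.8. This is fair, and it makes 328 the like-for-like comparison, with 333 as a cross-check. The calorie discrepancy is still more than ten times the largest of the other four.

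Two stronger readings are tempting. One is that the trial is underpowered for calorie intake; the printed inputs show the opposite. The other is that the correlation of 0.9 is the misprint; step 3 shows that no correlation up to 1.0 reaches 375 on its own.

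**Conclusion.** The stated 375 kcal is inconsistent with the inputs printed beside it. Assuming two-sided alpha 0.05 and a comparison of the two-visit mean, the detectable difference is about 328 kcal (333 by t), so 375 is 14.5% (normal) or 12.6% (t) too large. That it cannot be reached does not depend on how the visits are weighted, only on the alpha, power and n that the other four figures support.

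The cause is the result itself, a standard deviation, or a setting (n, alpha or power) that differs from what is printed. The article does not show which. If the printed inputs are right, the error is conservative and no conclusion about the adequacy of the sample changes. A reader might infer that the printed standard deviations are certainly too small; that is only one of the possible causes.

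**What to change.** Check the two standard deviations against the pilot data, and the n, alpha and power against the original calculation. If the printed inputs are right, replace 375 with about 330 kcal. If 375 came from other inputs, correct the standard deviation or setting that was misprinted. Stating the alpha, its sidedness and the use of the two-visit mean would let a reader verify all five figures. The cost is one corrected number or input and, at most, one added sentence; design, enrollment and analysis are unaffected.

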#### Physical activity adherence

Physical activity adherence is measured by accelerometer at months 3 and 6 as the number of minutes of moderate to vigorous intensity physical activity per week. Using data from a previous trial
[39], we assume a standard deviation of 142 minutes/week at months 3 and 6, with a correlation of 0.9 between the two time points. With 80% power and an n=30 in both groups, we will be able to detect a 100 minute/week difference between the two groups.

## Discussion

Obesity continues to be a significant public health issue worldwide and guidelines recommend intensive behavioral interventions for all obese adults
[1,2,40]. However, efficacious and scalable interventions have not yet been widely implemented. Mobile technology provides an opportunity to develop interventions with lower costs, less burden, and a greater reach, particularly as mobile usage rates continue to rise. As of February 2012, approximately 46% of American adults currently own a smartphone, an increase from 36% in May 2011
[26]. Minority groups, including Blacks and Hispanics saw an increase in smartphone use from 44% to 49% during this same time period
[26]. Smartphones have the ability to extend key components of intensive weight loss treatment into real-world settings, while reducing treatment costs and maintaining efficacious weight loss outcomes. The ENGAGED study is an innovative randomized controlled trial that will examine the feasibility and efficacy of a theory-guided, technology-supported weight loss program. Specifically, a total of 96 obese adults will be randomized to one of three conditions: a) Standard behavioral weight loss program (STND); b) technology-supported behavioral weight loss program (TECH); or c) self-guided behavioral weight loss program (SELF). Differences in weight loss, behavioral adherence, and goal attainment will be examined between groups.

The technology-supported condition will utilize a smartphone application designed to target known health behavior change mechanisms. Participants will be able to track weight and dietary intake, receive real-time feedback on behaviors, and communicate with team members by using a private message board and direct messaging. The application will also connect wirelessly via Blue-tooth to an accelerometer to provide real-time feedback on objectively measured physical activity. The ENGAGED technology will enable participants to experience ongoing support and accountability by allowing study coaches to continuously view participant’s up-to-date data, enabling them to provide timely support in the event of technical difficulties and tailored, immediate feedback during coaching calls.

Limited research has been conducted on smartphone-supported weight loss interventions, leaving numerous unanswered questions and directions for future research. Future studies are especially needed on the efficacy of mobile health interventions in underrepresented groups (i.e., older adults, ethnic minorities, uneducated, and low SES). Also needed are studies on the efficacy of technology supported interventions over the long-term, as weight loss maintenance continues to be one of the greatest challenges to obesity interventions
[41]. To date, there are few or no behavioral interventions that fully maintain weight losses after treatment ends
[42]. If the ENGAGED study provides preliminary evidence that a smartphone-supported intervention improves short-term weight loss and adherence outcomes, further studies will be warranted to examine whether the use of this technology can enhance long-term weight loss maintenance.

The ENGAGED Study is a theory-guided randomized controlled trial that will examine the efficacy and feasibility of a smartphone-supported implementation of the DPP on weight loss and behavioral adherence. Although smartphone usage is on the rise, the evidence base evaluating applications for health behavior change is extremely sparse. This study will make an important contribution by rigorously examining the effect of a novel, scalable smartphone technology system on self-monitoring adherence and weight loss outcomes.

